## 6. Evaluation Items

The timing of assessments during the continuous period will be identical to that in the comparative period.

### Note on Evaluations:

For the evaluation items “*Oral mucositis (CTCAE v3.0 subcriteria)*” and “*Pain NRS at the affected site*”, the efficacy of the investigational device is principally limited to the *designated affected site*—defined in inclusion criterion (3) as “a site where contact occurs between teeth and oral mucosa” (corresponding to the filled site in the intervention group).

Therefore, this site must be identified in advance on Day 1 for all participants, including the control group (which does not receive device filling).

If multiple affected sites are present, each must be assessed individually.

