## **4. Study Methods**

### **(1) Study Type and Design**

This is a multicenter, prospective, open-label, randomized, parallel-group comparative study.

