## ② Intervention Procedures

The comparative period (Day 1) begins on the day the investigational device is applied prior to chemotherapy. Chemotherapy should be initiated within three days after device placement (Day 0–3).

The evaluation timepoints are scheduled for Day 14, 21, or 28 of each treatment period, depending on the chemotherapy regimen.

After baseline assessments and interviews on Day 1 (before chemotherapy), interventions are conducted as follows:

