### **3. Full Registration and Randomization**

Following full registration in the EDC system, randomization information will be generated automatically through the same system, assigning each participant to either the intervention or control group.

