# **5. Observations and Assessment Items**

## **(1) Participant Background**

- Age at consent, medical history\*, comorbidities\*\*, primary disease classification (breast cancer), drug/food allergies, smoking history, alcohol consumption, and body weight.
- Presence and site of oral mucositis lesions (upper/lower labial vestibule, dorsal/right/left/ventral/tip of tongue, buccal mucosa).
- Planned date of starting the comparative period (Day 1) and details of concurrent chemotherapy regimen (agents, cycle presence, cycle duration).
- History of prior radiotherapy (excluding head and neck region) and timing.
- Presence of oral candidiasis.

\* **Medical history:** diseases clinically significant between 1 year prior to registration and enrollment, and other resolved conditions ( $\geq 1$  year before registration) judged relevant to participant background.

\*\* **Comorbidities:** diseases with ongoing symptoms at the time of registration.

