| re-screening for eligibility               | ○                                       |                                      |                                              |                                    |                                                                                                                                                                                                     |
| Obtaining informed consent                 | —                                       |                                      |                                              |                                    |                                                                                                                                                                                                     |
| Pre-registration and eligibility screening | ●                                       |                                      |                                              |                                    |                                                                                                                                                                                                     |
| Verification of subject background         | ●                                       |                                      |                                              |                                    |                                                                                                                                                                                                     |
| Final registration and randomization       | ●                                       |                                      |                                              |                                    |                                                                                                                                                                                                     |
| Interview / Physical examination / ECOG PS | ●                                       | ● c)                      | ●                                            | ●                                  | ●                                                                                                                                                                                                   |

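### The target site that decides the primary endpoint is identified on Day 1, after open-label randomisation, which leaves a risk of differential site selection between the arms

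*Protocol*

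**What the plan says.** Section 4(1) of the protocol fixes the masking: "This is a multicenter, prospective, open-label, randomized, parallel-group comparative study". The Schedule table in Section 5 marks the row "Final registration and randomization" only in the screening/enrolment column, whose window runs from Day −56 to Day −1. Under Section 4(7), once full registration is done, "randomization information will be generated automatically through the same system, assigning each participant to either the intervention or control group".

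Section 4(4) defines the later time point: "The comparative period (Day 1) begins on the day the investigational device is applied prior to chemotherapy". The Note on Evaluations in Section 6 limits the device's efficacy assessment to the designated site, defined through inclusion criterion 3 as a place where teeth touch the oral mucosa and glossed as "corresponding to the filled site in the intervention group". It then says: "Therefore, this site must be identified in advance on Day 1 for all participants, including the control group". It adds: "If multiple affected sites are present, each must be assessed individually".

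Both routes to success in Section 8(2), prevention of onset and improvement of grade, are defined at the target site.

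**The concern.** The site is part of the definition of the outcome. Its choice also sets the route by which a participant can succeed: a site with a lesion at baseline can succeed only by improving, and a clear site only by staying clear. If the person naming the sites knows the arm, then which sites are named, and how many, can differ between arms for reasons unrelated to the device. Randomisation balances the participants but not a choice made after allocation. This matters because it bears on the primary endpoint of a confirmatory trial. An analysis plan cannot supply a pre-allocation record that was never made.

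**Working it through.** **Order of events, from the protocol's own text**

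| Step | When | Source |
|---|---|---|
| Contact confirmed as an eligibility criterion | Screening | Sections 4(7), 10(1) |
| Lesion sites, oral findings and intraoral photographs recorded | Screening | Sections 5(1), 5(2) |
| Full registration and randomisation | Day −56 to Day −1 | Section 5, Schedule |
| Arm assigned by the EDC | Directly after full registration | Section 4(7) |
| Target site identified | Day 1 | Section 6, Note on Evaluations |
| Device applied (device arm) | Day 1 | Section 4(4) |
| Grade at the target site decides success | End of comparative period | Section 8(2) |

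Identification therefore comes before treatment and follow-up, but after allocation. No section describes a masked person naming the sites.

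**What is recorded before allocation.** Inclusion criterion 3 asks only whether contact exists. The background item "Presence and site of oral mucositis lesions" records lesions, and a participant with no mucositis has none to record. No item requires the contact site itself to be written down before registration.

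**Working criterion by arm.** In the device arm the target corresponds to the filled site, and Section 4(4) has the dentist fill the teeth judged to cause the mucosal injury. In the control arm nothing is filled during the comparative period, so only the contact definition applies. The nominal definition is shared, but the judgement that puts it into practice can differ.

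**The plan's own figure.** Inputs from Section 7: rates 50% and 25%, two-sided 5%, power 90%, Pearson chi-square, 1:1. With a mean rate of 0.375:

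n = [1.960·√(2·0.375·0.625) + 1.282·√(0.5·0.5 + 0.25·0.75)]² / 0.25²
= [1.960·0.6847 + 1.282·0.6614]² / 0.0625 ≈ 76.7, so 77 per group.

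The stated 77 per group reproduces. Approximate power is 90.1%. Exact enumeration of the same test gives 90.6%.

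**Illustration of what is at stake.** The shifts below are assumptions; the documents give none. There is no true device effect, and site choice alone adds a shift to the device arm's success rate. The rejection probability is the sum of Bin(x; 77, p₁)·Bin(y; 77, p₂) over all pairs (x, y) for which the two-sided Pearson test rejects at 5%.

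| Control rate | Shift 0 | +5 points | +10 points | +15 points |
|---|---|---|---|---|
| 25% | 5.0% | 10.7% | 27.2% | 51.5% |
| 37.5% | 5.3% | 10.1% | 24.1% | 45.6% |
| 50% | 4.5% | 8.8% | 23.0% | 47.1% |

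A shift against the device costs power instead. With a 25% control rate, a device rate of 45% rather than 50% reduces power from 90.6% to 75.2%, and 40% reduces it to 51.5%.

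**The case against.** The discretion is narrower than free choice. Section 6 gives one anatomical definition for both arms and requires every affected site to be assessed, and Section 4(4) requires all candidate teeth in the device arm to be filled and assessed. The Day 1 baseline comes before both the intervention and chemotherapy, so nobody can choose a site after seeing how it fared. Screening photographs and lesion records offer some pre-allocation evidence against which Day 1 sites could be checked.

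All of this stands, and it reduces the point to a risk of differential judgement. It does not remove the point. Assessing every declared site does not settle which sites, or how many, are declared, and a photograph is not a record of designated contact sites.

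A reader might infer that randomisation is undone for the primary endpoint. The text does not support that: the safeguards above are real, and nothing shows that selection will differ. A reader might also infer that naming a control site has no clinical consequence. Sections 4(3) and 4(4) say otherwise, since controls who continue chemotherapy receive the device by the same procedure in the continuous period.

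**Conclusion.** The point holds as a risk of bias. In an open-label trial, the location at which the primary endpoint is graded is fixed after the arm is known, and the criterion in use can differ between arms. That rests on the protocol's stated sequence and on no assumption. The size and direction cannot be derived from the documents. The error rates in the table depend wholly on the assumed shifts, and no stated figure in the protocol is wrong.

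Two stronger readings should be resisted.

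- A reader might infer that a participant with several sites succeeds if any one of them does. Section 8(2) does not say so. The only rule for several sites is the worst score, which points the other way, although it is listed under the secondary methods.
- A reader might calculate that one extra site moves success by about 19 points (0.75 − 0.75² = 0.1875). That needs an assumed 25% onset per site, independence between sites in one mouth, and an extra site in every participant of one arm only. With a correlation of 0.5 it halves to 0.094. If only 20% of one arm had an extra site, it would be 0.2 × 0.1875 = 0.0375. Under the worst-score rule, extra sites in the device arm would count against the device.

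**What to change.** Amend the Note on Evaluations and the Schedule so that all target tooth–mucosa contact sites are identified by one written criterion, the same for both arms, and locked in the EDC at screening, before full registration and randomisation. Use these sites for the primary endpoint in both arms, whatever is later filled, and on Day 1 only grade them. The wording that equates the target with the filled site must be reconciled with this. Which teeth are filled remains a clinical decision that the change does not touch. If several sites are locked, state that the worst-score rule of Section 8(2) also applies to the primary endpoint.

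The cost is one EDC entry moved ahead of randomisation and a few sentences of text; the oral examination and photographs are already planned at screening. Moving the identification does not change the 77 per group. Stating the worst-score rule makes explicit what the primary section leaves open, so the 50% and 25% assumptions should be checked against it; Section 7 does not say how the exploratory trial handled several sites. A small downside is that contact may change in the up to 56 days before Day 1. Record any change and examine it in a sensitivity analysis, without replacing the site. Participants randomised before the amendment will have no locked site and should be identified as such in the analysis.

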## (1) Primary Endpoint

### Oral mucositis severity based on CTCAE v3.0 subcriteria during the comparative period

| Grade                                                                                       | Description                                                                                                                                                                                                                                                                                                                                                |
|---------------------------------------------------------------------------------------------|------------------------------------------------------------------------------------------------------------------------------------------------------------------------------------------------------------------------------------------------------------------------------------------------------------------------------------------------------------|
| Grade 1
Erythema of the mucosa                                                           | 
 
Mucosal erythema and edematous changes without erosion or ulcer formation.
 
                                                                                                                                                                                                                               |
| Grade 2
Patchy ulcerations or pseudomembranes                                            | 
 
Patchy and localized, with each lesion measuring less than 30 mm in diameter.
 
“Localized” refers to an area that does not extend across multiple sub-sites.
 
Even when ulcers are present in multiple sub-sites, they are considered localized if they occur sporadically in each area.
 
 |
| Grade 3
Confluent ulcerations or pseudomembranes;
bleeding with minor trauma          | 
 
Lesions extending over a wide area measuring 30 mm or more in diameter.
 
Lesions spreading across multiple sub-sites (e.g., from the hard palate to the soft palate, or from the left to the right side of the tongue).
 
                                                                          |
| Grade 4
Tissue necrosis; significant spontaneous bleeding; life-threatening consequences | 
 
Ulcers or pseudomembranes spreading throughout the entire oral cavity.
 
Persistent bleeding from the ulcerative surface.
 
Extensive presence of coagulum-like crusts (excluding bleeding associated with detachment of superficial crusts caused by surface dryness).
 
                    |
| Grade 5
Death                                                                            |                                                                                                                                                                                                                                                                                                                                                            |

(Source: Oral Supportive Care Study Group, *Manual for the Evaluation of Oral Mucositis in Cancer Therapy, 1st Ed., OSC3, 2015.*)

- This CTCAE v3.0–based evaluation serves as the primary endpoint for the comparative period.
- In the continuous period, the same outcome will be treated as a secondary endpoint.
- When Grade 1 symptoms disappear, the condition will be recorded as “none (Grade 0 for convenience)”.

#### Rationale:

CTCAE v3.0 is a standardized, objective, and internationally accepted index for the evaluation of oral mucositis severity.

## (2) Secondary Endpoints

1. The same CTCAE v3.0–based oral mucositis evaluation conducted during the continuous period.
2. Mucositis oral according to **CTCAE v5.0 / MedDRA/J v25.1**.

| Grade | Description                                                                              |
|-------|------------------------------------------------------------------------------------------|
| 1     | Asymptomatic or mild symptoms; intervention not indicated                                |
| 2     | Moderate pain or ulcer that does not interfere with oral intake; modified diet indicated |
| 3     | Severe pain; interfering with oral intake                                                |
| 4     | Life-threatening consequences; urgent intervention indicated                             |
| 5     | Death                                                                                    |

### Oral pain according to CTCAE v5.0/MedDRA/J v25.1

| Grade | Description                              |
|-------|------------------------------------------|
| 1     | Mild pain                                |
| 2     | Moderate pain; limiting instrumental ADL |
| 3     | Severe pain; limiting self care ADL      |
| 4     | -                                        |
| 5     | -                                        |

- In oral pain (CTCAE v5.0), disappearance of pain is defined as “none (Grade 0)”.
- In oral mucositis (CTCAE v5.0), Grade 0 is not defined.

### 3. Quality of Life (QOL) Assessment [Patient-Reported Outcomes]

- PRO-CTCAE v1.0 (Items #3a and #3b)
- EORTC QLQ-OH15 (Item #35)
- Pain NRS at affected site

The *Pain NRS* will be derived from the patient diary and represents the maximum pain level during each treatment period.

The scale ranges from **0 to 10**:

- 0: no pain
- 1–3: mild pain
- 4–6: moderate pain
- 7–10: severe pain (10 = “unbearable pain, worst ever experienced”)

4. **Occurrence site and timing of oral mucositis**

Evaluated across all intraoral regions (upper/lower labial vestibule, tongue dorsum/right/left/ventral/tip, buccal mucosa, palate, others), and specifically at the designated affected site.

5. **Subgroup analyses** by chemotherapy regimen for preventive and pain-relieving efficacy.

6. **Chemotherapy completion status** (treatment adherence).

7. **Number of as-needed anti-inflammatory analgesic tablets** (from patient diary).

8. **Number of rescue uses of oral steroid ointment** (from patient diary).

9. **Use of Episil® oral liquid** (presence/absence; patient diary).

10. **Technical performance assessment**

Evaluation of natural, brushing-related, eating-related, and self-induced device dislodgement.

11. **Patient preference for continued use of the investigational treatment**

Evaluation of participants' willingness to continue using the device.

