## 240 **2) Comparative Period – Control Group**

241 (Standard care [oral care, Episil® oral liquid, etc.] only)

- 242 • Record the start date of the comparative period.
- 243 • Participants receive only standard care as per routine practice (see Section 6 for concomitant
- 244 treatments).
- 245 • After the comparative period evaluation, during the continuous period (Day 1–14/21/28), the
- 246 investigational device will be applied using the same procedure as the intervention group.
- 247 • Device removal, dislodgment recording, and discontinuation criteria are handled identically
- 248 to the intervention group.

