### **Comparative Period**

- Interview and physical examination.
- Hematology (as above).
- Blood biochemistry (as above).
- Pain and QOL scores (CTCAE v5.0 / v3.0, PRO-CTCAE #3a, 3b, EORTC QLQ-OH15 #35, pain NRS).
- Presence, site, and timing of oral mucositis.
- Presence and timing of oral candidiasis.
- Intraoral photographs.
- Confirmation of concomitant medications/therapies.

- Evaluation of procedural factors.
- Patient preference or acceptability of the investigational treatment.
- ECOG PS.
- Patient diary entries (once daily) including:
  - Device dislodgement (presence/absence),
  - Pain intensity (PRO-CTCAE #3a, #3b; EORTC QLQ-OH15 #35; pain NRS),
  - Number of as-needed anti-inflammatory analgesic tablets,
  - Number of uses of oral steroid ointment as rescue medication,
  - Use of *Episil*® oral liquid (yes/no).
- Adverse events.
- Device malfunctions.
- G-CSF administration (yes/no).

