**Timing of Assessments:**

- Items 1–5: Screening / registration, Day 1 of the comparative period, end (or discontinuation) of comparative period, and end of continuous period.
- Items 6–11: End (or discontinuation) of comparative period, and end of continuous period.

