**Rationale for Endpoint Selection:**

- Items 1–3 (excluding localized NRS): internationally standardized measures for QOL in oral mucositis.
- *Localized NRS*: captures pain limited to the specific mucosal site.
- Item 4: assesses overall oral mucositis occurrence.
- Items 5–9: necessary to evaluate efficacy of the investigational device.
- Item 10: required for assessing technical feasibility of device application.
- Item 11: necessary for evaluating patient acceptability and continued use.

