#### **Statistical Methods:**

- For items (1)–(2), analyses identical to those for the primary endpoint will be applied.
- For item (5), subgroup analyses by chemotherapy regimen will be performed similarly.
- For other items:
  - Categorical data: same as primary analysis (frequencies, percentages, chi-square).
  - Continuous data: summary statistics (as above), estimation of intergroup differences and 95% CIs, and use of two-sample Wilcoxon or two-sample t-tests depending on distribution.
  - Analyses will also be performed on *change from Day 1*.
  - *Pain NRS* will be analyzed both as a continuous variable and as categorical (0 = none, 1–3 = mild, 4–6 = moderate, 7–10 = severe).
  - For participants with multiple affected sites, the worst score per period will be used.

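### Secondary item 9 reduces daily Episil diary entries to presence/absence, so a reduction in days of use among users can be missed

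*Protocol*

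**What the plan says.** - **Endpoint.** Section 6(2), item 9, gives Episil use as "presence/absence; patient diary". Items 7 and 8, from the same diary, are counts: analgesic tablets and rescue uses of steroid ointment.
- **Data.** Section 5(2), Comparative Period, lists "Patient diary entries (once daily) including" several fields, one of them Episil "oral liquid (yes/no)". The continuous period repeats these assessments.
- **Timing.** Section 6(2), Timing of Assessments: "Items 6–11: End (or discontinuation) of comparative period, and end of continuous period".
- **Analysis.** Section 8(2)3): "Categorical data: same as primary analysis (frequencies, percentages, chi-square)". For continuous data the same section provides between-group differences with 95% CIs and "use of two-sample Wilcoxon or two-sample t-tests depending on distribution".
- **Purpose.** Section 6(2), Rationale for Endpoint Selection: "Items 5–9: necessary to evaluate efficacy of the investigational device".
- **Availability of Episil.** Control-group care in section 4(4) is "Standard care [oral care, Episil® oral liquid, etc.] only", and the intervention group receives the same care plus the device. Section 3 marks Episil with a plus/minus sign, and section 4(6) lists it only as an example of a permitted protectant.
- **Observation time.** Section 4(3) allows a comparative period of 14, 21 or 28 days, with 21 as standard.

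**The concern.** Up to 28 daily answers appear to become one yes or no per participant and period. A participant who needed Episil once and one who needed it every day then score the same. If the device leaves most users as users but lets them apply Episil on fewer days, the planned comparison is poorly placed to show it.

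The protocol's own background makes that kind of effect relevant: section 3 names the need for frequent self-application among Episil's limitations. That burden is one of frequency, and ever/never use does not measure it. The item is also declared necessary for judging efficacy, so a null result could be taken as evidence that the device does not reduce reliance on Episil.

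Ever-use also rises with the number of days observed, so the percentage mixes need for Episil with cycle length.

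**Working it through.** **1. The plan's own figure.** The only sample-size calculation, in section 7, concerns the primary endpoint: 50% v 25%, two-sided 5%, 90% power. With pooled variance under the null, n = [1.96·√(2·0.375·0.625) + 1.2816·√(0.5·0.5 + 0.25·0.75)]² / 0.25² = (1.342 + 0.848)² / 0.0625 ≈ 76.7, so 77 per group. This reproduces. No use rate or power is stated for Episil, so every use rate below is an assumption.

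**2. Dependence on observation time.** If each day carried an independent use probability p, ever-use over d days would be 1 − (1 − p)^d. For p = 10% this is 77%, 89% and 95% at 14, 21 and 28 days. Days within a person will be correlated, which lowers the level, but ever-use still rises with d.

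**3. Model for power.** There are 77 participants per arm and 21 diary days. A share u of each arm are potential users. Among these, days of use are beta-binomial with mean m and within-person correlation ρ = 0.1 or 0.3. With k = (1 − ρ)/ρ, a = (m/21)·k and b = (1 − m/21)·k, the chance that a potential user records any use is 1 − B(a, b + 21)/B(a, b).

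| m | ρ = 0.1 | ρ = 0.3 |
|---|---|---|
| 10 days | 99.8% | 95.9% |
| 6 days | 97.0% | 83.5% |

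**4. Worked case: 70% users in both arms, 10 v 6 days among users.** Ever-use is 0.70 × 99.8% = 69.9% v 0.70 × 97.0% = 67.9% (ρ = 0.1), or 67.1% v 58.4% (ρ = 0.3). For ρ = 0.3 the pooled rate is 62.75%. The null standard error is √(2·0.6275·0.3725/77) = 0.078, and 1.96 times this is 0.153. The standard error under the alternative is also 0.078. Power ≈ Φ[(0.087 − 0.153)/0.078] ≈ 20%. Mean days over the whole arm nevertheless fall from 0.70 × 10 = 7.0 to 0.70 × 6 = 4.2.

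**5. Simulated power.** Ranges run over ρ = 0.1 to 0.3 and simulation error.

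| Assumed effect (control → device) | Ever-use, chi-square | Days of use, Wilcoxon |
|---|---|---|
| All potential users, 10 → 7 days | 3–45% | 89–99.7% |
| 70% users in both arms, 10 → 6 days | 5–22% | 65–85% |
| 40% users in both arms, 10 → 6 days | 5–10% | 19–22% |
| 70% → 50% users, 10 → 7 days | 74–82% | 94–98% |
| 40% → 20% users, days among users unchanged | 75–77% | 73–75% |
| 90% → 70% users, days among users unchanged | 81–91% | 53–58% |

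The first row is near the ceiling. The second and third are not, so the loss there comes from collapsing the daily data. In the last two rows the device acts only on who starts Episil, and ever-use loses nothing or is clearly better.

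**The case against.** **Is there a ceiling?** Because Episil belongs to standard care in both arms, a reader might infer that nearly everyone will use it and that the endpoint cannot move. The documents do not support this. Episil is optional (sections 3 and 4(6)), patients apply it to an affected area, section 3 puts mucositis at about 40% of chemotherapy patients, and section 10(1) does not require mucositis at entry. A ceiling is a risk, not a fact.

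**Are days of use always better?** A reader might also infer that the share of days should replace ever-use. That follows only if the device acts solely on days among users. Prevention of onset is part of the primary responder definition in section 8(2)2), and a patient whose mucositis is prevented may never start Episil. The last two rows of the table show ever-use level or ahead. This objection stands and rules out demoting ever-use.

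**Is the collapsing rule stated?** No sentence says any use during the period. The label could simply echo the daily yes/no field, section 8(2)3) repeats the item without it, and end-of-period timing also covers items 7 and 8, which are counts. An analysis plan that is not shown could define days of use. This stands in part: ever/never is the natural reading rather than an explicit rule. But the protocol itself sets the binary form for item 9 while giving its neighbours as counts, so this is not merely a detail left open.

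**Does cycle length bias the comparison?** No. Allocation is randomised 1:1 and the standard period is the same in both arms. Cycle length affects the level and meaning of the percentage; only chance imbalance would carry it into the contrast.

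**Is it important?** It is one of eleven secondary items, with no stated power. That limits the weight of the point.

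**Conclusion.** The point holds in a limited form. As written, item 9 most naturally becomes ever/never use per period, which can miss a reduction in days of use among users. With 70% users in both arms and mean days falling from 10 to 6, power is about 5–22% against 65–85% for days of use. If both starting and days fall, days of use also does better. If only starting is prevented, ever-use is similar or stronger. The protocol does not say which mechanism to expect, so neither measure is sufficient alone.

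The figures rest on assumed use rates, beta-binomial days with correlation 0.1 to 0.3, a 21-day period and complete diaries. They show direction and rough size, not the trial's actual power. Only this secondary endpoint is affected; the primary analysis and the 77 per group are not.

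**What to change.** In section 6(2), item 9, and section 8(2)3), add a second measure: the proportion of completed diary days in the period on which Episil was used. Compare it between arms with the Wilcoxon test and report the difference with its 95% CI, both of which section 8(2)3) already provides for continuous data. Keep the ever/never comparison beside it, and state explicitly that it means any recorded use during the period. Using completed diary days as the denominator allows for 14-, 21- and 28-day periods and early discontinuation.

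The cost is wording in two places and one more secondary comparison. The daily entries are already collected, so no visit, form or patient burden is added. The number of applications per day cannot be recovered from a yes/no field, and the text should not suggest otherwise. As the trial is open-label, the definition is best fixed before outcome data are examined.
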